## Abstract

**Background:**

Poor adherence to treatment is common in patients on hemodialysis which may increase risk for poor clinical outcomes and mortality. Self management interventions have been shown to be effective in improving compliance in other chronic populations. The aim of this trial is to evaluate the effectiveness of a recently developed group based self management intervention for hemodialysis patients compared to standard care.

**Methods/Design:**

This is a multicentre parallel arm block randomized controlled trial (RCT) of a four session group self management intervention for hemodialysis patients delivered by health care professionals compared to standard care. A total of 176 consenting adults maintained on hemodialysis for a minimum of 6 months will be randomized to receive the self management intervention or standard care. Primary outcomes are biochemical markers of clinical status and adherence. Secondary outcomes include general health related quality of life, disease-specific quality of life, mood, self efficacy and self-reported adherence. Outcomes will be measured at baseline, immediately post-intervention and at 3 and 9 months post-intervention by an independent assessor and analysed on intention to treat principles with linear mixed-effects models across all time points. A qualitative component will examine which aspects of program participants found particularly useful and any barriers to change.

**Discussion:**

The NKF-NUS intervention builds upon previous research emphasizing the importance of empowering patients in taking control of their treatment management. The trial design addresses weaknesses of previous research by use of an adequate sample size to detect clinically significant changes in biochemical markers, recruitment of a sufficiently large representative sample, a theory based intervention and careful assessment of both clinical and psychological endpoints at various follow up points. Inclusion of multiple dependent variables allows us to assess the broader impact on the intervention including both hard end points as well as patient reported outcomes. This program, if found to be effective, has the potential to be implemented within the existing renal services delivery model in Singapore, particularly as this is being delivered by health care professionals already working with hemodialysis patients in these settings who are specifically trained in facilitating self management in renal patients.

**Trial registration:**

Current Controlled Trials ISRTN31434033

## Background

End stage renal disease (ESRD) is a complex disease associated with compromised quality of life (QoL), unplanned hospital admissions, high mortality and therefore high burden of illness [1,2]. With rising prevalence worldwide, the growth of ESRD populations has been a concern for many countries, as ESRD consumes increasing proportions of healthcare budgets [3,4]. The burden of ESRD will increase with the growth of the ageing population [5,6] and increased prevalence of diabetes [7].

As in other countries the incidence and prevalence of ESRD in Singapore is rising [7]. The incidence rate has inflated from 194.0 per million population (pmp) to 284.9 pmp from 1999 to 2007 [8]. This increase has been standardized for age differences between the population cohorts and hence is an underestimate as there is an escalation in the elderly population of Singapore. Singapore has one of the fastest aging populations in the world. When elderly is defined as a person of 65 years of age and above, the number of elderly has expanded from 47,200 in 1965 to 330,000 in 2009 [9]. This rapid expansion of the elderly in Singapore will have a significant effect on rates of ESRD.

Mortality is high among patients receiving renal replacement therapy with an 8% mortality rate in the first 90 days [10]. In Singapore, survival during the first year of dialysis is 89.3% and 58.7% after a period of 5 years [9]. Risk factors for mortality include older age, physical and nutritional impairment, smoking, prior myocardial infarction, low serum albumin levels at baseline, catheter access at first dialysis, concomitant cancer, heart failure, depression, HIV/AIDS, lung disease, neurological disease, psychiatric conditions and late referral to a Nephrologist [11,12].

Cardiovascular disease (CVD) accounts for approximately 50% of all deaths [13]. Dialysis patients are on average at approximately 30 times higher risk of a fatal cardiovascular event than the general population, and this risk still remains 10 to 20 times higher after stratification for age, gender and diabetes [13]. This burden of CVD has been associated with both traditional risk factors such as smoking, diabetes, hyperlipidaemia, hypertension and physical inactivity and non-traditional chronic kidney disease-associated factors such as anaemia, hyperhomocystenaemia, oxidative stress and bioincompatibility [14]. Several investigators have identified associations between elevated serum phosphate, calcium × phosphate product, parathyroid hormone and death in hemodialysis patients [15]. Interventions that lower serum phosphate levels and thereby delay the development of secondary hyperparathyroidism may reduce cardiovascular mortality.

Hemodialysis requires radical lifestyle changes including regular attendance at the dialysis unit for treatment, restrictions in fluid intake, changes to diet and medication intake. Estimates within the haemodialysis population suggest that the prevalence of non-adherence is between 10% to 60% for fluid intake, 2% and 57% for dietary advice, between 0 and 35% skip or shorten dialysis sessions and between 19% and 99% are non-adherent to their medications [16]. This is likely to be associated with psychosocial variables such as patients' beliefs about medication, social support, and personality characteristics rather than clinical or sociodemographic variables [17,18]. Poor adherence can have a significant impact on the risk of morbidity and mortality. In one large scale study, when compared to compliant patients, those who skipped one or more hemodialysis sessions in a month had 5.7% greater interdialytic weight gain and higher serum phosphate levels. Those who had shortened the duration of 3 or more of their hemodialysis sessions over the period of one month had a between a 13% and 35% higher risk of death [19]. It has been estimated that each 1-mg/dL increment in phosphate level increases relative and cardiovascular mortality risk by 5% and 10% respectively [20,21]. Especially when phosphate levels are > 5.5-6.0 mg/dL, mortality risks start to increase considerably [21,22].

Self management interventions offer an effective tool to support adjustments to the lifestyle changes required in hemodialysis. For self management to be effective, it needs to encompass the patient's ability to monitor their condition and to affect the cognitive, behavioural and emotional responses necessary to maintain a satisfactory QoL [23]. There are 5 core self managements skills; problem solving, decision making, resource utilization, forming of a patient/heath care provider partnership and taking action [24].

Although there is evidence to suggest both clinical and psychological benefits resulting from self management interventions in chronic conditions such as arthritis, diabetes and recurrent lower urinary tract infections [25-27], there is comparatively less work on the value of self management programs in renal disease.

Cross sectional research within the Chronic Kidney Disease (CKD) population [28] and with kidney transplant patients [29] has shown that perceived self efficacy is a more consistant correlate of the performance of self management behaviours than clinical and demographic variables. In addition engagement in self management behaviours has been associated with improved QoL [30]. There have however been very few randomised controlled trials assessing the impact of self management in hemodialysis. Adaptation training and patient empowerment programs with patients on hemodialysis have been shown to reduce perceived stress, depression and improve self care self-efficacy and QoL at 3 to 6 months post intervention [31-33]. A group based intervention using cognitive behavioural techniques to enhance effective self management of fluid consumption has also been shown to improve interdialytic weight gains although these effects were evident only at 14 weeks follow up [34]. Although these studies suggest that psychosocial interventions increase adherence and improve success in self-care in the context of hemodialysis, most have been underpowered, the interventions are poorly described, follow up duration is limited and rigorous evaluation through the inclusion both clinical and psychological outcomes data are lacking. Reviews have also criticized these studies for not describing in detail the required training, content or theoretical background for the intervention and intervention delivery and fidelity [35-38].

The proposed study will address weaknesses of previous research by recruitment of a sufficiently large and representative hemodialysis sample, the development of a well designed theory driven and evidence based intervention and the inclusion of validated assessments of both clinical and psychological outcomes up to 9 months post intervention. In doing so this trial will provide much needed data on the efficacy of self management interventions with respect to clinical and psychological outcomes that can inform clinical practice and health care services.

This paper describes the design, setting, intervention and outcomes of the NKF-NUS program, a 36 month cluster randomised trial of self-management support program for prevalent hemodialysis patients.

### Study Objectives

1. To implement a group based self management intervention for patients on hemodialysis

2. To undertake an evaluation of this self management intervention comparing it with "standard care". The primary aim is to determine the efficacy of the self management intervention on biochemical markers of clinical status and adherence. Secondary aims are to determine the effect impact on QoL, mood, self-efficacy and patient satisfaction.

## Methods/Design

### Trial design

The study design (Figure 1) is guided by the CONSORT statement [39]. The NKF-NUS Study is a 3 year pragmatic cluster randomized clinical trial to evaluate whether hemodialysis patients benefit from a self management intervention. The study protocol has been approved by the NUS Institutional Review Board and is in compliance with the Helsinki declaration.

**Figure 1 F1:**
[figure not shown]
**Flow Chart of Study Design**.

Participants will be randomized based on dialysis shift within each of the participating NKF dialysis centres into one of two groups;

Group 1: Standard care control group - care currently received by patients as defined by the National Kidney Foundations Clinical Practice Guidelines. All healthcare resources used and advice given to prevalent patients relating to their kidney failure and its treatment will be standardised.

Group 2: Group based self management intervention

Patients from both arms will be assessed with the same measures and at the same time intervals over the study period.

### Setting and Centre Recruitment

The study will be conducted at the National Kidney Foundation (NKF) dialysis centers, Singapore. There are 24 NKF dialysis centres in Singapore providing hemodialysis to more than 2100 ESRD patients. These are located throughout the island to ensure easy community access to patients residing in different parts of Singapore. NKF Dialysis centres are nurse led with a multidisciplinary team of renal consultants, medical social workers, dieticians and exercise specialists on rotation.

Of these 14 NKF dialysis centres will be included in the program. Although random selection of dialysis centres would have been preferable this was not an option due to the lack of facilities in their excluded dialysis centres to either host the intervention in situ or their considerable distance to other dialysis centres with available facilities. Location and proximity to intervention venues was an important parameter to take into account as the intervention sessions are scheduled over weekends and hence require substantial commitment on the part of patients and dialysis centre staff.

### Participants

The senior nurse manager in each of participating dialysis centres, will screen patients for eligibility and provide a list of eligible patients and their preferred language of communication to the research coordinator. A research assistant (RA) proficient in the patients' preferred language of communication (e.g. English, Mandarin, or Malay) will then approach eligible patients for participation. Participants will be given an information sheet outlining the details of the study and the RA will subsequently verbally explain the study procedures and requirements, and provide clarifications as needed.

Following written informed consent, participants will be requested to undertake a baseline assessment (Time 1) (comprising the self report questionnaires listed in the following section) prior to group allocation (intervention vs. control). Follow up assessments will be taken immediately after the end of self management intervention (Time 2) and at 3 months (Time 3) and 9 months post intervention (Time 4) (See Figure 1).

Inclusion criteria are:

(1) Chronic Kidney Disease patients who have been receiving hemodialysis for at least 6 months

(2) Aged 21 and over

(3) Patients willing to attend all sessions of the self management programme.

Exclusion criteria are:

(1) Newly established on hemodialysis (< 6 months)

(2) Unable to give informed consent

(3) Unable to understand spoken English and/or Mandarin, Malay, Tamil dialects to allow effective communication with the intervention facilitator(s) and/or Research assistants

(4) A diagnosis of functional psychosis or organic brain disorder

(5) Impaired cognition

(6) Major visual or hearing impairments, or other sensory or motor impairments that may prohibit completion of the scheduled assessments

(7) Unable to participate in a group program (e.g. housebound)

(8) Limited life expectancy due to co-morbid illness such as malignancy

### Randomization

Cluster randomization will take place whereby patients within the participating dialysis units will be randomised according to the days on which they receive dialysis. For example, within a centre those dialysing on Monday, Wednesday and Friday will receive the intervention and those dialysing on Tuesday, Thursday and Saturday will serve as controls. This will prevent cross contamination of information between groups, a problem encountered when studying participants who spend large amounts of their time together in a closed environment.

Once a block of 30 participants have provided informed consent and completed baseline assessment, randomization will be performed by the study coordinator, using a computerized method to avoid assignment bias. Due to the nature of the study and in common of studies if this type, patients will not be blinded to their group allocation. Primary outcome measures will be assessed by a research associate blinded to treatment allocation and uninvolved in consenting and the management of the patients. Health care professionals and dialysis personnel involved in patients' care will also be blind to group allocation. It is not however deemed possible to keep project staff tracking data collection for secondary outcomes (self reported outcomes) blinded to condition so the trial will only have double blind accuracy with respect to primary outcomes. However, as questionnaire assessments are by self-report, rather than rated by a member of the research team, significant influences of observer biases are not expected.

### Participant withdrawal of consent to research follow-up

If a participant withdraws their consent whilst in the trial, one of the study team will contact the participant to determine if they are willing for the data they have given up to that point to be included in the trial. No data will be used in the analysis without a participant's consent.

### Sample calculation

Using serum phosphate levels as a physiological index of adherence to diet and medication) and Kidney disease specific QoL as primary outcomes, a total sample size of 126 and 128 respectively, were calculated. This was using 80% power (alpha = 0.05) to detect a significant absolute change of 1.5% in phosphate control and of 5 points (0.5 standard deviation) in the physical and mental component subscale scores in kidney disease QoL short form questionnaire [40]. Taking the larger number of 128 participants (64 in intervention and 64 in control group), a final total number of 154 participants (77 in each group) is needed to ensure at least an 80% final response rate is met (attrition/drop-out rate estimated at 20%). A target sample of 154 participants will be sought.

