#### Primary outcome measures

Beginning at baseline (Time 1) and continuing into follow up (Time 2, Time 3, Time 4) regular chart reviews will be conducted to abstract clinical, laboratory, and pharmacological data including:

(1) Interdialytic weight gain: The amount of weight gained between the end of one dialysis session and the beginning of the next. This is a validated marker of adherence to fluid restriction/regulation.

(2) Blood pressure

(3) Serum phosphate and calcium × phosphate product indicating a patient's adherence to prescribed oral phosphate binder medications and dietary phosphate restriction.

(4) Serum potassium indicating adherence to dietary recommendations.

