### Statistical Considerations

Outcomes will be analysed immediately after the intervention and then at 3 and 9 months

separately on an intention to treat basis. Analyses of covariance (ANCOVAs) will be performed for each outcome to examine changes within groups (Intervention vs. standard care control) comparing baseline to follow-up assessments. Covariates used will include baseline levels and other casemix differences between the groups (if any). The statistical significance criterion will be set at *P *< 0.05.

In addition to this intention-to-treat analysis we will also undertake a "per protocol" analysis on those individuals who attended all of the educational sessions in the intervention arm.

No formal subgroup analyses are planned. However exploratory analysis of the impact of patient level factors (e.g. age, gender, ethnicity and time on dialysis) on the effect of the intervention will be carried out.

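### The primary outcome is not fixed: kidney-specific QoL is primary in the sizing and secondary elsewhere, and five unranked primary markers are each tested at three visits at P < 0.05

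*Protocol article*

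**What the plan says.** **Sizing.** The Sample calculation treats two outcomes as primary: "Using serum phosphate levels as a physiological index of adherence to diet and medication) and Kidney disease specific QoL as primary outcomes". It reports that "a total sample size of 126 and 128 respectively, were calculated", and carries the larger figure, the one for QoL, forward. The phosphate basis is "This was using 80% power (alpha = 0.05) to detect a significant absolute change of 1.5% in phosphate control". The QoL basis is "5 points (0.5 standard deviation) in the physical and mental component subscale scores in kidney disease QoL short form questionnaire". Alpha is not divided between the two outcomes, or between the two QoL component scores.

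**Status of QoL elsewhere.** The abstract states: "Secondary outcomes include general health related quality of life, disease-specific quality of life, mood, self efficacy and self-reported adherence". Study Objectives puts QoL among the secondary aims. The Randomization section equates the secondary outcomes with the self-reported ones. The KDQoL-SF is the first item under Secondary process and outcome measures.

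**Primary list.** The Primary outcome measures section gives four numbered items holding five markers: interdialytic weight gain, blood pressure, serum phosphate, calcium × phosphate product and serum potassium. Phosphate and the product share one item: "Serum phosphate and calcium × phosphate product indicating a patient's adherence to prescribed oral phosphate binder medications". No marker is named as the lead.

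**Testing rule.** Statistical Considerations says: "Outcomes will be analysed immediately after the intervention and then at 3 and 9 months", and the sentence goes on to say that this is done separately. Each outcome gets its own ANCOVA. "The statistical significance criterion will be set at" P < 0.05. No visit is named as primary, and no order of testing or adjustment is given. The abstract describes a different analysis, mixed models that span all assessments.

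**The concern.** Two statements in the current text cannot both be true: QoL is primary, and QoL is secondary. An analysis plan not shown here could choose one of them, but it could not reconcile them. The choice also affects blinding. The Randomization section claims blinded assessment for primary outcomes only and concedes that staff handling the self-reported outcomes cannot be kept blind. If QoL is primary, that assurance does not cover it.

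The second problem is the testing rule. With five unranked primary markers, three visits and one unadjusted threshold, a null intervention has many chances to yield a significant primary result. The text does not prevent a claim of efficacy on whichever marker and visit looks best. This is more than detail left to a longer document, because the article states the threshold and the visit-by-visit testing explicitly.

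**Working it through.** **1. Reproduce the plan's figure.** Inputs from Sample calculation: difference 5 points, equal to 0.5 SD (so SD = 10), power 80%, alpha 0.05, 1:1 allocation. Two-sided testing is assumed, since sidedness is not stated.

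- Normal approximation: n per arm = 2 × (1.960 + 0.842)² × 10² / 5² = 62.8, so 63 per arm and 126 in total.
- t-test version: 63.8, so 64 per arm and 128 in total. Power at 64 per arm is 0.801.

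The stated 128 for QoL is reproduced. The stated 126 for phosphate cannot be rebuilt, because the 1.5% change comes with no SD or base rate.

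**2. Effect of the QoL label on N.** 128 − 126 = 2 participants before dropout. With the factor of 1.2 that takes 128 to 154 (128 × 1.2 = 153.6), phosphate alone would give 126 × 1.2 = 151.2.

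**3. Count the tests under Statistical Considerations.** 5 markers × 3 post-baseline visits = 15. If systolic and diastolic pressure were tested separately, 6 × 3 = 18, but the article says only blood pressure.

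**4. Chance of at least one false-positive primary result.** For k independent tests at 0.05 it is 1 − 0.95^k. Because the tests are correlated, this is an upper reference. The correlated figures come from simulated normal test statistics (200,000 draws, two-sided 0.05) with equal correlation between markers and equal correlation between visits. All correlations are assumed.

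| Assumption | 15 tests | 18 tests |
|---|---|---|
| Independent | 0.537 | 0.603 |
| Markers 0.3, visits 0.5 | 0.455 | 0.513 |
| Markers 0.3, visits 0.7 | 0.411 | 0.461 |
| Markers 0.5, visits 0.7 | 0.361 | 0.405 |
| Markers 0.7, visits 0.8 | 0.270 | 0.297 |

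**5. The same under the abstract's mixed model, read as one test per marker.**

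- Five independent tests: 1 − 0.95⁵ = 0.226.
- Six independent tests: 1 − 0.95⁶ = 0.265.
- Five tests with phosphate and its product correlated at 0.9 and all other pairs at 0.2 (same kind of simulation): 0.197.

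The range is about 20% to 26%. If every pair of markers were correlated at 0.7, the most extreme case in step 4, it would be about 15%.

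**6. Price of keeping all five as primary at one visit.** Holm's first step compares the smallest p-value with 0.05/5 = 0.01. For a 0.5 SD effect and 64 completers per arm, power at 0.01 is 0.59. Restoring 80% needs 192 completers.

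**The case against.** The strongest reply has four parts.

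- **The abstract's mixed model may reduce the test count to one per marker.** This stands as a qualification, and the lower range in step 5 reflects it. It does not remove the problem. The abstract conflicts with Statistical Considerations and names no primary contrast, and 20% to 26% is still four to five times 5%.
- **No success rule is stated.** This also stands. A reader might infer that a significant result on any one of 15 to 18 tests would count as success, or that the true error rate is 54% to 60%. The document supports neither. It gives a threshold for significance, not a criterion for efficacy, and independence cannot hold when one marker is a product containing another and the visits are repeated measurements on the same patients. What can be said is that no criterion excludes a claim on the best result.
- **The QoL label hardly matters for size.** This stands. A reader might infer that the trial is sized on a variable that plays no part in judging success. But phosphate, a listed primary marker, was sized too and gave 126 against 128.
- **A condensed article can leave the lead visit and multiplicity to a fuller document, and the Discussion presents multiple outcomes as deliberate.** The silence on a lead visit alone would not be a finding. The contradictory status of QoL and the explicit unadjusted rule are statements, not silences.

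**Conclusion.** The point holds in limited form. The status of kidney-specific QoL is contradicted within the current text: one section makes it primary and four places make it secondary. The stated rule of separate ANCOVAs at three visits, applied to five unranked primary markers at P < 0.05, inflates the chance of a false-positive primary result well above 5%. How far depends on which analysis description governs and on correlations that the document does not give: roughly 27% to 46% for 15 tests under the correlations assumed here, with 54% as the independence ceiling, and about 20% to 26% if the mixed model gives one test per marker. That inflation is present on every reading examined is secure; its exact size is not. The consequence of the QoL label for sample size is negligible on the plan's own figures. Its consequence for what is confirmatory, and for the blinding claim, is real.

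**What to change.** - **Name one primary marker and one primary time point**, tested at two-sided 0.05. Serum phosphate is the only outcome called primary by both the sizing section and the primary list. Nine months is one option, given the Discussion's interest in whether effects last. Sample calculation names no visit, so the choice is the sponsor's, to be made before any outcome data are seen.
- **Make the other markers secondary**, tested under Holm only if the primary is significant. Without that gate, the overall error across primary and secondary tests is not held at 5%. Report the other visits as estimates with confidence intervals.
- **Choose one analysis** and state it identically in the abstract and in Statistical Considerations.
- **Label KDQoL as secondary in Sample calculation**, to match the rest of the article.
- **Restate the sample size on the chosen primary**, with its SD or base rate. For phosphate this needs information that the article does not give, so this step is more than rewording.

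The main cost is that fewer results can be called confirmatory. If several primaries are kept instead, apply Holm across them at the one visit and restate the power. With five primaries and 128 completers it is about 0.59 at the first step for a 0.5 SD effect, so that route means either accepting lower power or enlarging the trial.

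### Dialysis shifts within centres are randomised, but the sample size and the stated ANCOVA make no allowance for correlation within a shift

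*Protocol article*

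**What the plan says.** **Unit of randomisation.** Trial design calls the study a "3 year pragmatic cluster randomized clinical trial", and the end of the Background uses the same label. The text under Figure 1 says: "Participants will be randomized based on dialysis shift within each of the participating NKF dialysis centres into one of two groups". Randomization repeats it: "Cluster randomization will take place whereby patients within the participating dialysis units will be randomised according to the days on which they receive dialysis". The reason given there is to stop information passing between patients who spend much of their time together. Setting and Centre Recruitment gives the number of centres: "Of these 14 NKF dialysis centres will be included in the program".

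**Sample size.** Sample calculation says: "This was using 80% power (alpha = 0.05) to detect a significant absolute change". For quality of life the change is 5 points, or 0.5 SD. This gives 128 patients (64 per arm), raised to 154 for 20% attrition. The section gives no ICC, cluster size, cluster count or design effect.

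**Analysis.** Statistical Considerations specifies an ANCOVA for each outcome, separately at each follow-up, with P < 0.05. On covariates it says: "Covariates used will include baseline levels and other casemix differences between the groups (if any"). Neither shift nor centre is mentioned.

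**Abstract.** Its Methods/Design paragraph describes a "multicentre parallel arm block randomized controlled trial (RCT"), with 176 patients and linear mixed-effects models over all time points. It names no cluster effect.

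**The concern.** The protocol relies on patients of one shift being in close contact to justify allocating whole shifts. It then sizes the trial, and states its analysis, as if each patient had been allocated separately.

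When shifts are allocated, variation between shifts becomes part of the error of the treatment comparison. A patient-level ANCOVA without a shift term leaves that part out. If outcomes within a shift are correlated, its standard errors are too small and an ineffective programme is declared effective more than 5% of the time. The sample size has the matching fault, because it counts correlated patients as independent. This affects both arms and is separate from any further clustering created by group sessions in the intervention arm.

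**Working it through.** **Inputs from the protocol:** difference 0.5 SD, power 80%, alpha 0.05, 128 analysed (64 per arm), 20% attrition, 14 centres.

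**Assumptions:** a two-sided test; shift-level ICC from 0.01 to 0.10; two day patterns per centre, so 14 × 2 = 28 shifts. The two patterns appear in Randomization only as an example.

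**1. Reproducing the plan's figure.** By the normal approximation, n per arm = 2(1.960 + 0.842)²/0.5² = 62.8, so 63. The t-test solution is 63.77, so 64 per arm and 128 in total, with power 80.1%. The stated 128 is therefore exactly the figure for individual randomisation, with design effect 1.

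**2. Slack.** 154 × 0.8 = 123 analysed, which gives 78.6% power even at ICC 0. The abstract's 176 × 0.8 = 141 analysed, and 141/128 covers a design effect of only about 1.10.

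**3. Design effect with 28 shifts.** m = 128/28 = 4.57 and DE = 1 + (m − 1) × ICC. Power comes from the noncentral t with noncentrality 0.5 × √(64/(2 × DE)). It is shown with 126 df (128 − 2) and with 13 df (14 centre pairs − 1). It refers to a test with the correct standard error and no baseline adjustment. Type I error when clustering is ignored is 2[1 − Φ(1.96/√DE)].

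| Shift ICC | DE | Power, 126 df | Power, 13 df | Type I error |
|---|---|---|---|---|
| 0.01 | 1.036 | 79% | 73% | 5.4% |
| 0.05 | 1.179 | 73% | 67% | 7.1% |
| 0.10 | 1.357 | 67% | 61% | 9.2% |

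At ICC 0.05 the difference detectable with 80% power is 0.54 SD on 126 df and about 0.58 SD on 13 df.

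**4. Fewer, larger clusters.** Randomization waits for a block of 30. If a block is split into two shifts, 154/30 is about five blocks, or 10 clusters. Then m = 12.8, and at ICC 0.05 DE = 1 + 11.8 × 0.05 = 1.59. Type I error is 12.0% and power about 60% before any degrees-of-freedom penalty. A simulated centre-paired analysis with five centres and 13 patients per shift had about 41% power.

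**5. Direction of the error.** Both arms lie within each centre. For an analysis that omits shift and centre, the ratio of true to assumed variance is about 1 + (m − 1) × ICC(shift) − ICC(centre). Simulated type I error of the unadjusted patient-level comparison, with 14 centres and 5 patients per shift:

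| Centre ICC | Shift ICC | Type I error |
|---|---|---|
| 0.05 | 0 | 4.6% |
| 0 | 0.05 | 7.4% |
| 0.05 | 0.05 | 6.9% |
| 0 | 0.10 | 9.9% |

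A centre-paired analysis stayed between 4.8% and 5.2% in all seven ICC settings run with 14 centres.

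**6. Baseline adjustment.** With baseline–outcome correlation r, and the ICC unchanged by adjustment, the variance is multiplied by (1 − r²). At r = 0.5 and ICC 0.05 the factor is 1.179 × 0.75 = 0.884, so power is about 85%, or 79% with 13 df. On the large-sample scale the loss is cancelled when r = √(1 − 1/DE), which is 0.39 at ICC 0.05 and 0.51 at ICC 0.10. True and assumed variance shrink by the same factor, so the type I error in step 3 does not change.

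**The case against.** Much of the case on the other side stands and limits the point.

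- **Any clustering inflates the error.** A reader might infer this, but the documents do not support it. Arms are compared within centres, so centre-level correlation largely cancels (step 5). Nothing says that nurses or machines belong to one shift, and Setting and Centre Recruitment describes the care team at centre level. Placing the whole ICC on the shift, as step 3 does, is the least favourable split.
- **The planned analysis has less than 80% power.** This too goes further than the documents. The 64 per arm is an unadjusted figure, while the ANCOVA adjusts for baseline, which could offset the loss (step 6). What is shown is that the calculation as written does not fit the design.
- **The analysis rules out a cluster term.** The covariate sentence is not exhaustive, and the abstract does not list random effects. Such detail is often left to an analysis plan, which is not shown. The Discussion also intends to look at differences between shifts. That does not correct the variance, but it shows that shift differences were considered.
- **The effect may be small.** With 28 shifts and an ICC of 0.02 or less, type I error is at most 5.8%.

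The mismatch itself survives. The protocol states both a sample size and a model, and neither as stated matches the unit that it randomises. The sample-size part does not depend on how the model wording is read.

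**Conclusion.** The concern holds in this form: shifts are randomised, the sample size has design effect 1, and the analysis as stated contains no shift or centre effect. The nominal 5% error is not assured. It is exceeded if there is shift-level correlation, and the test is slightly conservative if all correlation lies at centre level.

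That the mismatch exists is certain; its size is not. It rests on an assumed ICC and a cluster count that the protocol leaves unclear. It ranges from minor (28 shifts, ICC 0.01) to serious (about 10 clusters, ICC 0.05). The power figures apply to the unadjusted calculation, and baseline adjustment may restore some or all of that loss. Because the error rate of the primary comparison is at stake and the remedy is cheap, this should be corrected before analysis.

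**What to change.** 1. **Statistical Considerations and abstract:** specify one model in both places. Include effects for centre and for shift within centre, plus patient where visits are modelled together, with Kenward-Roger or Satterthwaite degrees of freedom. Support it with a permutation test that swaps shift labels within centre. State how many shifts are allocated: with five pairs there are only 2⁵ = 32 arrangements, so the smallest two-sided P is 2/32 = 0.0625.
2. **Sample calculation:** keep the target, and restate the power over a stated ICC range on the same degrees of freedom as the planned analysis. For example, at ICC 0.05 with 28 shifts, 128 analysed and no baseline adjustment: about 67% power for 0.5 SD, or 80% power for about 0.58 SD. Show any gain from baseline adjustment separately, under a stated correlation. The targets of 154 and 176 need reconciling at the same time.
3. **Abstract:** describe the trial as cluster randomised.

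The cost is wider intervals and a less favourable stated power. No extra patients or data are needed, since allocation by shift within centre means that both are known for each patient.
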